### Outcome Measures

#### Outcome Assessment and Schedule

The outcome indicators are derived from WHO IYCF indicators [49,50]. Outcome data will be collected using structured interviewer-administered questionnaires and anthropometric assessments at predefined follow-up visits. The schedule of outcome measurements is presented in Table 2.

**Table 2. T2:** Schedule of enrollment, interventions, and assessments of participants as per SPIRIT (Standard Protocol Items: Recommendations for Interventional Trials).

Study steps	Baseline	Postallocation						
		Birth	6 wk	10 wk	14 wk	6 mo	9 mo	12 mo
Enrollment and allocation								
Eligibility screen	✓^a^							
Informed consent	✓							
Randomization	✓							
Allocated intervention								
mHealth^b^ coaching	mHealth coaching will occur continuously across the study period with the SoC^c^, not just at specific time points							
Face-to-face counseling	✓	✓	✓	✓	✓	✓	✓	✓
Participants characteristics								
Maternal	✓							
Infant		✓						
IYCF^d^ knowledge, attitude, and breastfeeding self-efficacy								
Baseline (at enrollment)	✓							
Midline (14th wk)					✓			
Endline (12th mo)								✓
Study outcome								
Early initiation of breastfeeding		✓						
Exclusive breastfeeding^e^			✓	✓	✓	✓^e^		
Continuation of breastfeeding at 1 y			✓	✓	✓	✓	✓	✓
Introduction of age-appropriate complementary feeding^e^						✓^e^	✓	
Minimum dietary diversity						✓	✓	✓
Minimum meal frequency						✓	✓	✓
Minimum acceptable diet						✓	✓	✓
Anthropometry		✓	✓	✓	✓	✓	✓	✓
Acute respiratory infection			✓	✓	✓	✓	✓	✓
Acute diarrhea			✓	✓	✓	✓	✓	✓
Visit to emergency room			✓	✓	✓	✓	✓	✓
Hospitalization			✓	✓	✓	✓	✓	✓
mHealth usability								
Assessment								✓

a ✓ indicates step conducted or outcome measured at the specific time point.

b mHealth: mobile health.

c SoC: standard of care.

d IYCF: infant and young child feeding.

e The 6-month assessments of exclusive breastfeeding and age-appropriate complementary feeding will serve as the primary outcome.

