#### Primary Outcomes

The primary end points of the study are (1) EBF at 6 months of infant age and (2) introduction of AACF [49,50] at 6 months of infant age.

In addition, EBF will also be assessed at the 6th, 10th, and 14th weeks, while CF practices will also be assessed at 9 months of infant age. The repeated assessments at additional time points will be used for longitudinal analyses to evaluate trends and sustainability of feeding practices over time. Operational definitions of the primary outcome measures are provided in Table 3.

**Table 3. T3:** Operational definitions of primary and secondary outcome measures.

Outcome	Operational definitions
Primary outcomes [49,50]	
Exclusive breastfeeding	Proportion of infants who are fed exclusively with breast milk up to 6 months of age
Introduction of age-appropriate complementary feeding	Proportion of infants who are introduced to solid, semisolid, or soft foods at 6 mos of age
Secondary outcomes	
Infant and young child feeding practices [49,50]	
Early initiation of breastfeeding	Proportion of children put to the breast within 1 hour of birth
Minimum dietary diversity	Proportion of children 6‐12 months of age who receive food from 4 or more food groups
Minimum meal frequency	Average number of daily meals for children 6‐12 months of age, who receive solid, semisolid, or soft foods
Minimum acceptable diet	Composite variable based on meal frequency and dietary diversity
Mean duration of breastfeeding	Average duration an infant is breastfeeding for 12 months
Continued breastfeeding at 1 y	Proportion of children 12 months of age who are still on breast milk
Child health	
ARI^a^	Short, rapid breathing that is chest-related and/or difficult breathing that is chest-related. Percentage of children up to 1 year of age with symptoms of ARI at any time in the last 2 weeks preceding the follow-up
Acute diarrhea	Passage of 3 or more loose or liquid stools per day (or more frequent passage than is normal for the individual). Percentage of children up to 1 year of age with symptoms of diarrhea at any time in the last 2 weeks preceding follow-up
Visit to the emergency room	Infant brought to the emergency room for management of any acute illness in past 2 weeks.
Hospitalization	Infant admitted to the hospital for diagnosis or management of any acute illness in past 2 weeks.

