### Statistical Analysis

#### Data Analysis Plan

Baseline characteristics will be summarized by randomized group using frequencies and percentages for categorical variables (eg, education, socioeconomic status, area of residence, and employment status) and mean (SD) or median (IQR) for continuous variables (eg, maternal age and parity), as appropriate. Normality of continuous variables will be assessed using the Shapiro-Wilk test. Baseline comparability will be evaluated using chi-square or Fisher exact tests for categorical variables and independent-samples *t* tests or Mann-Whitney *U* tests for continuous variables.

All primary and secondary analyses will follow the intention-to-treat principle, including all participants as randomized. Primary outcomes (EBF and AACF at 6 mo of infant age) are binary and will be analyzed using regression models appropriate for dichotomous outcomes. The results will be expressed as adjusted risk ratios or odds ratios with 95% CIs. Treatment effects will be reported with corresponding 95% CIs and 2-sided *P* values. Repeated measures of EBF (at the 6th, 10th, and 14th weeks) and CF practices will be analyzed using mixed-effects regression models with random intercepts to account for within-participant correlation and fixed effects for treatment group, time, and group-by-time interaction.

Secondary outcomes that are binary, including EIBF, continued breastfeeding at 1 year, MDD, MMF, and MAD, will be analyzed using similar logistic regression approaches. Continuous secondary outcomes, including mean duration of breastfeeding and child anthropometric *z* scores (height-for-age, weight-for-height, and weight-for-age), will be analyzed using linear regression or linear mixed-effects models, with results reported as mean differences and 95% CIs.

Breastfeeding self-efficacy and mHealth usability will be measured using validated multi-item Likert-scale instruments. Composite scale scores will be generated by summing or averaging item responses and analyzed as continuous outcomes using linear or mixed-effects linear regression models, as appropriate. Distributional assumptions will be assessed, and robust standard errors or nonparametric methods will be applied in sensitivity analyses if substantial departures from normality are observed.

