The extent and patterns of missing data will be examined. If more than 10% of outcome data are missing, multiple imputation using chained equations will be performed under a missing-at-random assumption. Imputed results will be compared with complete-case analyses in sensitivity analyses. Prespecified subgroup analyses will assess effect modification by maternal education, employment status, and parity through inclusion of interaction terms. All analyses will be conducted using Stata software (StataCorp), with statistical significance set at .05.

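### If exclusive breastfeeding is scored since birth, the random-intercept model planned for weeks 6, 10 and 14 has, on a logistic link, no finite estimate; the scoring should be stated and the model replaced

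*Protocol article*

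**What the plan says.** Table 3 of the Protocol article defines EBF once: "Proportion of infants who are fed exclusively with breast milk up to 6 months of age". Table 2 schedules EBF at weeks 6, 10 and 14 and at 6 months, with 6 months primary. The Primary Outcomes section says the additional visits serve to describe trends and sustainability over time.

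For EBF at the three early visits, and for complementary feeding, the Data Analysis Plan says that the repeated data "will be analyzed using mixed-effects regression models with random intercepts to account for within-participant correlation". The fixed part of the model has terms for arm, visit and their interaction. The visits listed for EBF stop at week 14, and no link function is named in that sentence. The surrounding text calls the primary outcomes binary, reports risk ratios or odds ratios, and says binary secondary outcomes "will be analyzed using similar logistic regression approaches". Linear mixed models are named only for continuous outcomes.

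On scoring, Outcome Assessment and Schedule says "The outcome indicators are derived from WHO IYCF indicators". No recall period is given for the EBF question at the early visits. Table 3 does give a two-week window for respiratory infection, diarrhoea, emergency visits and hospitalisation.

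**The concern.** A status that can be lost but not regained allows only four response patterns over weeks 6, 10 and 14: 111, 110, 100 and 000 (1 = still exclusively breastfed). A random-intercept logistic model treats the three visits as independent given the infant's intercept. At any finite intercept SD it therefore gives positive probability to patterns that cannot occur, such as 010 or 101. The fit improves only by making the SD larger, without limit.

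Sustained feeding is the contribution that the Introduction and Discussion claim for this trial, and this model is the planned analysis of it for EBF before 6 months. If it is fitted to such data, the software will either fail to converge or stop at an arbitrary point and print odds ratios that describe the numerical settings rather than the intervention.

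**Working it through.** The article gives no figure for this model, so there is none to reproduce. The check uses illustrative data.

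**Inputs.**
- From Sample Size: 150 per arm and 20% loss, so 150 × 0.80 = 120 per arm.
- Assumed, not in the article: EBF at weeks 6, 10 and 14 of 80/70/60% in control and about 90/84/78% with the app, strictly monotone.
- Control pattern counts: 000, 24; 100, 12; 110, 12; 111, 72.
- Intervention pattern counts: 000, 12; 100, 7; 110, 7; 111, 94.

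**Model.** logit P(EBF at visit k, arm a | u) = b(a,k) + s·u, with u standard normal. Group, categorical time and their interaction give six free coefficients, three per arm.

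**Step 1: the ceiling.** The saturated log-likelihood is the sum of n·ln(n/120) over the four patterns in each arm.
- Control: 24 ln 0.20 + 2 × 12 ln 0.10 + 72 ln 0.60 = −38.63 − 55.26 − 36.78 = −130.67.
- Intervention: 12 ln 0.10 + 2 × 7 ln(7/120) + 94 ln(94/120) = −27.63 − 39.78 − 22.95 = −90.36.
- Total, unrounded: −221.0357.

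**Step 2: the profile over s**, coefficients maximised at each value on a dense grid.

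| Intercept SD | Log-likelihood | Week-6 arm log-OR | Week-14 arm log-OR |
|---|---|---|---|
| 1 | −315.82 | 0.94 | 1.08 |
| 3 | −249.77 | 1.66 | 1.97 |
| 5 | −233.19 | 2.49 | 2.95 |
| 10 | −223.50 | 4.64 | 5.47 |
| 20 | −221.22 | 8.94 | 10.65 |
| 40 | −221.037 | 17.62 | 21.23 |

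From SD 80 upwards the value equals −221.0357 to the digits shown, and the coefficients double each time the SD doubles. As s grows with the coefficients scaled to it, visit k is 1 exactly when u exceeds −b(a,k)/s. Three ordered cut-points per arm reproduce any four monotone pattern frequencies. The ceiling is therefore approached but never reached, and no finite maximum exists. Linear time behaves the same way, with limit −221.2232.

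**Step 3: dependence on numerical settings.** With the SD held at 40, non-adaptive Gauss-Hermite quadrature gives these week-14 arm log-ORs:
- 7 points: 2.09 − 1.22 = 0.87.
- 15 points: 32.98 − 0.87 = 32.11.
- Dense grid: 31.37 − 10.14 = 21.23.

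**Step 4: short recall with a few returns.** In each arm, r infants move from 111 to 101 and r from 000 to 010, which leaves every per-visit proportion unchanged.

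| r | Fitted SD | Conditional OR, week 14 | Marginal OR, week 14 |
|---|---|---|---|
| 1 | 8.8 | 119 | 2.41 |
| 3 | 5.5 | 22 | 2.41 |
| 6 | 3.6 | 8.8 | 2.41 |

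**Step 5: alternatives on the monotone data.**
- Marginal, week 14: 94/120 against 72/120. RR = 0.783/0.600 = 1.31, OR = (94/26)/(72/48) = 2.41, difference 18 points.
- Discrete-time cessation risks: control 24/120, 12/96, 12/84; intervention 12/120, 7/108, 7/101.

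All of these are finite.

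**The case against.** The strongest reply is that divergence needs two premises that the article does not fix. It never says that the week 6, 10 and 14 answers cover the time since birth; indicators derived from WHO definitions could be asked with short recall, and returns to EBF would then be possible. Nor does it name a logit link for this model. A reader might infer that the planned model is certain to fail. The documents do not support that: with returns the logistic maximum is finite, and a linear mixed model would also give finite estimates. This part of the objection stands, and the point is conditional because of it.

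It does not remove the point. Table 3 writes a recall window where one is meant and gives EBF none, and the text around the model points to logistic regression. Step 4 also shows that a few returns leave conditional odds ratios many times the marginal ones. Such values are legitimate for a conditional estimand, but readers would take them for a very large effect.

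Four further inferences are tempting and should not be drawn:
- **The missing 6-month visit is an error.** It is largely a choice of scope. That visit has its own primary regression, and adding it would not cure the divergence.
- **Infants known to have stopped would be imputed as possible successes.** The rule reads "If more than 10% of outcome data are missing, multiple imputation using chained equations will be performed under a missing-at-random assumption". It does not say that such infants are imputed, and if EBF is scored since birth their 6-month value is already known to be no.
- **Breastfeeding duration is mishandled by linear regression.** Table 3's wording reads naturally as a mean restricted to 12 months, and no passage scores last contact as the end of breastfeeding.
- **Complementary feeding has the same defect.** The plan models feeding practices broadly, and diversity and meal frequency can rise and fall.

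**Conclusion.** The point holds in conditional form. On the only EBF definition given, with since-birth scoring at each early visit and a logit link, the stated model has no finite maximum-likelihood estimate. This follows from the pattern structure and does not depend on the assumed rates. If scoring allows a few returns, estimates exist, but with an intercept SD of about 4 to 9 and week-14 odds ratios of 8.8 to 119 against a marginal 2.41. Those sizes do rest on the illustrative rates and on 1 to 6 infants per arm in each return pattern.

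The consequence is confined to the supporting longitudinal analysis of sustained EBF. The primary comparisons at 6 months use a separate regression and are untouched. The change is worth making but is not critical to the trial's main conclusion.

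**What to change.** 1. State whether EBF at weeks 6, 10 and 14 and at 6 months is scored since birth or as point prevalence with a named recall period.
2. Replace the random-intercept model for EBF with one of two analyses over weeks 6, 10 and 14 and 6 months: a marginal (GEE) model, which suits either scoring, or, if EBF is scored since birth, a discrete-time or interval-censored time-to-cessation model. Report the arm difference in the proportion still exclusively breastfed at each visit.
3. If EBF is scored since birth, say in the derivation of 6-month EBF that an infant already recorded as stopped counts as no before any imputation. This makes explicit what the definition already implies.

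The cost is a few sentences of analysis-plan wording and a small amount of analysis work; no new data are needed. One trade-off should be noted: an unweighted GEE needs a stronger missing-data assumption than a likelihood-based model, so if dropout is appreciable it should be weighted or combined with the planned imputation. The article expects follow-up to finish by June 2027 and analysis by September 2027, so the choice can be fixed before any comparison by arm.

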Despite modest progress, significant gaps persist in Pakistan’s infant and young child feeding (IYCF) indicators. The recent National Nutritional Survey reported improvements in EIBF from 40% (2011) [10] to 45% (2018) [3]; yet, nearly 40% of neonates continue to receive prelacteal feeds [3], undermining the benefits of colostrum feeding. Further, a nonlinear trend was found in EBF, decreasing from 50% (2001) [3] to 37.7% (2011) [10] before rising to 48% (2018) [3], reflecting inconsistent policies and nonsustainable interventions. The decline in EBF was particularly evident at 3 months of infant age, dropping from 84% to 70% [11], reportedly due to inadequate maternal knowledge about EBF and its associated benefits [12]. The continued breastfeeding practice at 1 year also declined from 77.3% (2011) [10] to 68.4% (2018) [3], with only 40.1% of children aged 0 to 23 months receiving age-appropriate breastfeeding [3]. This means that while initial breastfeeding practices may be improving, their maintenance and adherence remain inadequate and challenging. Further, the complementary feeding (CF) indicators were even more concerning. Only 36% of children aged 6‐8 months receive timely CF; minimum dietary diversity (MDD) is achieved by 14%, minimum meal frequency (MMF) by 18%, and a mere 3.6% of children meet the minimum acceptable diet (MAD) criteria [3], a composite indicator reflecting both meal frequency and diversity. These significant deficiencies impair infant physical growth, immunity, and cognitive development.

This alarming situation has not improved much, as a recent study conducted in rural Sindh Province reported that <10% of infants were EBF, with a significant proportion identified as wasted (14.7%), stunted (36.7%), and underweight (38.5%) at birth [13]. The study also found a significant association of early initiation of CF or breast milk alternatives before 4 months and increased odds of wasting by 6 months of age (adjusted odds ratio 4.14, 95% CI 1.95-8.77; *P*<.001) [13]. This further reflects persistent gaps in early child nutrition, which are the result of a complex interplay of inadequate maternal knowledge, sociocultural norms and myths, and insufficient nutritional counseling at health system touchpoints [14-16].

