### Sample Size

The sample size was calculated to detect a 20% absolute difference in the primary outcomes between the intervention and control arms. The calculation assumed a baseline prevalence of EBF of 48% [3] and AACF of 50% [39] in the control group. Using a 2-sided significance level of 5%, statistical power of 80%, a 1:1 allocation ratio, and an anticipated 20% loss to follow-up in each study arm, a total sample of 300 pregnant women (150 per arm) was determined to be sufficient to detect the expected intervention effect. Loss to follow-up included participant withdrawal and/or discontinuation of app use in the intervention arm. Sample size estimation was performed using *OpenEpi* software (version 3.0).

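### Mean duration of breastfeeding is assigned to linear models, which cannot use the lower bound that is all that is known for infants lost while still breastfed

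*Protocol article*

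**What the plan says.** - **Model.** The Data Analysis Plan lists "Continuous secondary outcomes, including mean duration of breastfeeding and child anthropometric" z scores together and says that they "will be analyzed using linear regression or linear mixed-effects models, with results reported as mean differences and 95% CIs". It names no time-to-event or restricted-mean method for duration.
- **Outcome.** Table 3 defines mean duration of breastfeeding as "Average duration an infant is breastfeeding for 12 months". The natural reading is a duration capped at the 12-month visit.
- **Loss.** Sample Size allows for "an anticipated 20% loss to follow-up in each study arm" and adds: "Loss to follow-up included participant withdrawal and/or discontinuation of app use in the intervention arm".
- **Missing data.** The Data Analysis Plan states: "If more than 10% of outcome data are missing, multiple imputation using chained equations will be performed under a missing-at-random assumption". The imputed results are to be compared with complete cases.
- **Data available.** Table 2 schedules breastfeeding status at 6, 10 and 14 weeks and at 6, 9 and 12 months. The Follow-Up section allows collection by telephone or at a later facility visit.

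**The concern.** Time to stopping breastfeeding is a time-to-event outcome. A linear model needs one completed number per infant. An infant lost at 5 months while still breastfed does not supply one, since all that is known is that the duration is at least 5 months.

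The longer an infant is breastfed, the more likely it is that loss comes before the stop. Infants with a known duration are therefore a selected, shorter-duration group, even when loss is purely random. An imputation that treats duration as a single missing value learns from that group, so it carries the selection forward.

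Two things are at stake. The reported mean would be too low, and any difference in loss between arms would become a difference in duration. Only one arm can be lost by stopping app use, so unequal loss cannot be ruled out here.

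**Working it through.** The plan gives no figure for this outcome, so there is none to reproduce.

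**Inputs from the article:** 68.4% breastfed at 1 year (Introduction, a national survey figure); 20% loss (Sample Size); 12-month horizon (Table 3).

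**Assumptions:** constant stopping rate; a fraction q lost evenly over 0 to 12 months, independently of stopping; a stop that precedes loss is known.

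**1. True value.** λ = −ln(0.684)/12 = 0.03165 per month. The restricted mean is R = (1 − 0.684)/0.03165 = 9.98 months.

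**2. No loss.** The ordinary mean of durations capped at 12 is the same 9.98, although 68.4% of infants sit at the cap. Those infants do no harm to the mean.

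**3. Why missingness depends on duration.** An infant with duration t has a known value with probability 1 − q × min(t, 12)/12. At q = 0.20 this is 0.95 for t = 3, 0.90 for t = 6 and 0.80 for t = 12 or more. The share known only by a lower bound is q × R/12 = 0.20 × 9.984/12 = 16.6%.

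**4. Mean over known durations.** This is [(1 − q)R + qA] / [(1 − q) + q(1 − R/12)]. Here A = ∫₀¹² t λe^(−λt)(1 − t/12) dt = 0.6305 and 1 − R/12 = 0.1680.

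| q | Numerator / denominator | Mean (months) |
|---|---|---|
| 0.15 | 8.581 / 0.8752 | 9.80 |
| 0.20 | 8.114 / 0.8336 | 9.73 |
| 0.25 | 7.646 / 0.7920 | 9.65 |

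At 20% loss the shortfall is 9.98 − 9.73 = 0.25 month. A simulation of 2,000,000 infants, with loss at a constant rate instead of evenly, gives 9.74.

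**5. Unequal loss, no true effect.** 15% versus 25% gives 9.805 − 9.654 = 0.15 month. In the simulation, 10% versus 30% gives 9.87 − 9.58 = about 0.3 month.

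**6. Equal 20% loss, true effect.** If 68.4% versus 78.4% continue to 12 months, the true difference is 10.65 − 9.98 = 0.67 month. The known-duration means in the simulation differ by 10.47 − 9.74 = about 0.74 month, a small distortion.

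**7. Alternatives (simulation, 68.4% at 12 months, true value 9.98).** In the last column, mothers who stop before 12 months have twice the loss hazard, and actual loss is 25%.

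| Estimate | Independent loss, 20% | Loss related to stopping |
|---|---|---|
| Known durations only | 9.74 | 9.81 |
| Only infants followed to 12 months | 9.98 | 10.28 |
| Kaplan-Meier restricted mean | 9.98 | 10.09 |

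Under independent loss, the Kaplan-Meier restricted mean stays at 9.98 at 10%, 20% and 30% loss.

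**The case against.** The best defence is that the plan already handles missing outcomes. Expected loss of 20% would trigger the imputation rule if it is loss of outcome data, and visits can be replaced by telephone contact. Restricting to infants followed to 12 months is unbiased when loss is independent of stopping. The detail of how a cut-short duration enters the imputation often sits in an analysis plan that is not shown.

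Much of this stands. Imputing visit-level status, or respecting the lower bound, would repair the problem, and the article does not exclude either. But the point does not rest on the missing detail. It rests on the stated choice of a linear model on one completed duration. For that variable, missing at random fails by construction (step 3). Restricting to 12-month completers is safe only if loss is unrelated to stopping.

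Stronger readings are tempting, and the article does not support them:

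- **That about 68% of infants are censored and so bias the mean.** Under the 12-month horizon they have a known value (step 2). The result is a 12-month restricted mean, not total duration.
- **That last-contact time will be entered as the duration.** This would give about 9.0 months at 20% loss, but no section states it, and the imputation rule points elsewhere.
- **That the mean will be taken only over infants who stopped.** This would conflict with the commitment to analyse all participants as randomized.
- **That unequal loss is expected.** The plan expects 20% in each arm, and that figure includes stopping app use, which need not mean a missing outcome. The 15% versus 25% split is my assumption.

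**Conclusion.** The point holds in limited form. A linear model is a poor choice for a duration that loss will cut short, and the stated imputation does not by itself correct it. At 20% random loss the mean over known durations is about 0.25 month too low. An imbalance of 15% versus 25% produces a false difference of about 0.15 month, set against 0.67 month for a true rise from 68.4% to 78.4% continuing.

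These sizes rest on a constant stopping rate, a national prevalence that may not apply to this hospital, and assumed timing of loss. If much of the 20% is app discontinuation with outcomes still collected, the effect shrinks. Severity is low to moderate: one secondary outcome, with no bearing on the primary analyses.

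**What to change.** Remove mean duration of breastfeeding from the linear-regression list and add a sentence on these lines: restricted mean duration of breastfeeding to 12 months will be estimated in each arm from the survival curve, with infants lost while still breastfed censored at last contact. Stopping times will be taken from the reported stop date or treated as interval-censored between visits. The between-arm difference will be reported with its 95% CI.

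The method still assumes that loss is uninformative given what is modelled (10.09 versus 9.98 in step 7), so keep a missing-data sensitivity analysis. If imputation is used there, state that it works on visit-level breastfeeding status or respects the observed lower bound.

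The cost is one or two sentences. The method is standard, the status data are already scheduled at every visit from 6 weeks to 12 months, and follow-up is still under way.

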### Retention Strategy

The RA will remain engaged with all study participants fortnightly to maintain contact, confirm continued participation, and address any study-related or technical concerns. Participants in the intervention arm will be inquired regarding application functionality and, if necessary, provided assistance with troubleshooting or reinstallation of the app to ensure uninterrupted access. For participants in the control arm, the RA will maintain equivalent contact to minimize differential attention across study arms. Follow-up windows will remain flexible to accommodate participant availability, and alternative contact modalities will be used where needed. Attrition will be continuously monitored, and reasons for withdrawal will be documented. If attrition exceeds anticipated levels, this will be addressed analytically through intention-to-treat analyses, supported by sensitivity analyses using appropriate methods for missing data.

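### Imputation of missing primary outcomes is switched on only above 10% missing; at or below that the intention-to-treat analysis in effect becomes complete-case, and the roles of the two results are not fixed

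*Protocol article*

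**What the plan says.** Four statements in the protocol article bear on missing primary outcomes.

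- Data Analysis Plan, analysis population: "All primary and secondary analyses will follow the intention-to-treat principle, including all participants as randomized". The two primary outcomes, EBF and age-appropriate complementary feeding (AACF) at 6 months, "are binary and will be analyzed using regression models appropriate for dichotomous outcomes".
- Data Analysis Plan, missing data: "If more than 10% of outcome data are missing, multiple imputation using chained equations will be performed under a missing-at-random assumption". The next sentence reads: "Imputed results will be compared with complete-case analyses in sensitivity analyses". Nothing is said about 10% or less, or about whether the 10% is counted overall, per arm or per outcome.
- Retention Strategy: "If attrition exceeds anticipated levels, this will be addressed analytically through intention-to-treat analyses, supported by sensitivity analyses" that use suitable missing-data methods. No percentage is given.
- Sample Size: the calculation allows for "an anticipated 20% loss to follow-up in each study arm", and it defines loss broadly: "Loss to follow-up included participant withdrawal and/or discontinuation of app use in the intervention arm".

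The schedule table also has EBF recorded at weeks 6, 10 and 14, before the 6-month endpoint. Table 3 defines EBF as exclusive feeding over the whole period to 6 months.

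**The concern.** The imputation rule is written into the article, so this is not detail left to an unseen analysis plan. Its trigger is the amount of missing data. Bias depends on which mothers are missing and on whether that differs between arms. The trial is unblinded, the Limitation section expects app engagement to fall over the year, and only app-arm mothers can drop out because of the app. Loss related to feeding status in one arm is therefore plausible at any overall percentage.

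Below the trigger, a regression on a single 6-month outcome uses only mothers who have that outcome. Some of those dropped may already have a recorded feeding history that settles or strongly predicts their result. Above the trigger, imputation runs, but the article does not say whether the imputed or the complete-case estimate is the primary one. At stake is which number is reported as the effect on EBF and AACF, and whether selective loss under 10% is ever corrected.

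**Working it through.** **1. The two triggers as counts.** With 300 randomized, 10% is 30 women and 20% is 60. The 20% is the Sample Size figure; the Retention Strategy refers only to an expected level. Power is not the issue here: with 120 retained per arm, power for 48% versus 68% is 0.886.

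**2. How often each line is crossed.** Number missing ~ Binomial(300, true loss):

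| True loss | P(more than 30 missing) | P(more than 60 missing) |
|---|---|---|
| 8% | 0.087 | <0.0001 |
| 10% | 0.45 | <0.0001 |
| 12% | 0.84 | <0.0001 |
| 15% | 0.993 | 0.008 |
| 20% | >0.9999 | 0.47 |

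Near 10% loss, the choice of method is close to a coin toss. At the planned 20%, imputation would almost surely run, provided that planned loss means missing outcomes.

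**3. Selective loss below the trigger (assumed rates).** EBF at 6 months is 48% control and 68% app: the planning value and the planned 20-point gain. Assumed: EBF at week 14 is 70% control and 82% app, week-14 status is known for all, and EBF at 6 months requires EBF at week 14. Assumed loss: control 5% regardless of status; app 5% if still EBF at week 14 and 30% if not.

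- App retained: 0.82×0.95 + 0.18×0.70 = 0.779 + 0.126 = 0.905, so 9.5% missing. Overall: (5 + 9.5)/2 = 7.25%, about 7.3%. This is under 10% whether counted overall or per arm.
- Complete-case app rate: 0.68×0.95/0.905 = 0.646/0.905 = 71.4%. Control stays at 48.0%.
- Difference: 23.4 points against a true 20, a bias of 3.4 points. SE = √(0.48×0.52/142.5 + 0.714×0.286/135.75) = 0.057, so the bias is 0.59 SE.

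**4. The same case using the week-14 record.** Count mothers already off EBF at week 14 as failures, even if they are lost later.

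- App: 0.646/(0.779 + 0.18) = 0.646/0.959 = 67.4%.
- Control: 0.48×0.95/(0.70×0.95 + 0.30) = 0.456/0.965 = 47.3%.
- Difference: 20.1 points, a bias of 0.1.

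Each arm's rate is still slightly low (67.4 against 68; 47.3 against 48), because only mothers still on EBF at week 14 remain missing. Imputing them from week-14 status within arm restores 68% and 48% under these assumptions.

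**5. No true effect (assumed).** Both arms 70% at week 14 and 48% at 6 months, with the same loss rates.

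- App retained: 0.70×0.95 + 0.30×0.70 = 0.875, so 12.5% missing in the app arm and 8.75% overall.
- Complete-case app rate: 0.456/0.875 = 52.1%, a bias of 4.1 points. SE 0.060; bias/SE = 0.68; two-sided rejection rate about 0.105 instead of 0.05.
- Counting week-14 failures gives 47.3% in both arms and no bias in the difference.

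Here an overall count does not trigger imputation and a per-arm count does. The text allows either.

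**6. Above the trigger, where the roles are open (assumed).** Rates as in step 3, but control loss 20%, and app loss 10% if EBF at week 14 and 40% if not.

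- App retained: 0.82×0.90 + 0.18×0.60 = 0.846. Overall missing: (20 + 15.4)/2 = 17.7%.
- Complete-case difference: 0.612/0.846 − 0.48 = 24.3 points. Imputation from week-14 status gives 20.

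The two results differ by 4.3 points, and the article does not say which is primary.

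**The case against.** A reader might infer that the article holds two conflicting rules: that between 10% and 20% missing one demands imputation and the other demands nothing, and that above 20% they disagree on the main result. The documents do not support this. The Data Analysis Plan concerns missing outcome data; the Retention Strategy concerns attrition. The 20% does not appear in the Retention Strategy, and in the Sample Size section loss includes stopping app use, so a mother who abandons the app but attends at 6 months counts as lost yet has an outcome. The Retention Strategy does not forbid imputation below its level, and the Data Analysis Plan never calls imputation the main analysis. Both passages can be followed at once. That objection stands.

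Other fair points stand in part:

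- Complete-case at 10% or less is inferred. No other method is named, however, and a single-timepoint regression without imputation has no other way to treat a missing outcome.
- If missing outcomes reach 20%, imputation is almost certain, so the lower branch matters only if retention beats that figure.
- The threshold is fixed in advance and does not depend on treatment results, and the plan does say that missing-data patterns will be examined. Nothing links that examination to the choice of method.
- Telephone follow-up and fortnightly contact in both arms may limit loss. The loss rates above are assumed.
- Complete-case and imputation largely agree when missingness depends only on covariates in the model. Week-14 feeding is measured after randomization, so it would not be among the baseline confounders in the primary model. An imputation model can use it.
- A mother known to have stopped EBF by week 14 is already a failure under Table 3, which removes most of the illustrated bias. The article does not state this derivation, so the point supports the fix.
- Roles of imputed and complete-case results are often set in an analysis plan. This one may do so; the article's two passages should still agree with it.

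**Conclusion.** The point holds as a fault in a stated rule. Imputation is conditional on more than 10% of outcomes being missing. At or below that, the primary analysis is in effect complete-case, which does not fit the commitment to include everyone randomized. The Retention Strategy adds a second trigger that is unreconciled with the first but not contradictory to it, and the standing of the imputed and complete-case results is left open.

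The size is illustrative: a bias of 3.4 points (0.59 SE) at 7.3% missing, and a two-sided error rate of about 10% at 8.75% missing with no true effect. Both rest on assumed week-14 rates and on loss that depends on feeding status in the app arm only. They are not predictions, and no figure was worked out for AACF. They show that staying under 10% does not by itself protect the estimate, and that feeding data already scheduled would remove most of the bias for EBF.

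**What to change.** Remove the 10% trigger from the Data Analysis Plan and align the Retention Strategy with it, so that both describe one approach at any level of missingness:

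- The primary analysis of both primary outcomes includes all randomized participants, by multiple imputation within arm from baseline data and week 6, 10 and 14 feeding status.
- EBF is counted as failed, without imputation, where an earlier visit already recorded that it had stopped, in line with Table 3. This step does not apply to AACF, which relies on imputation.
- Complete-case is a sensitivity analysis, together with one missing-not-at-random analysis, for example counting missing outcomes as failures. In step 3 of the working that gives 0.646 − 0.456 = 19.0 points.

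The cost is a change of wording in two sections and a little more analysis work. No new data are needed. Follow-up is expected to run to June 2027, so this can be settled before outcomes are analysed.
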